### Intervention

Intervention general practices will be supported to implement a new service model incorporating quality incentives for patients’ relational continuity and timely access. The intervention itself will comprise a mechanism of, firstly, patient enrolment within a practice. The practice will then offer enrolled patients: a) guaranteed access to a minimum of three longer appointment types over the study period for older patients or those with chronic or complex illness; b) a review visit within 7 days of admission to an emergency department or hospital, or after other significant health events; and c) for patients aged less than 16 years, same day access for acute conditions.

Figure 2 summarises the incentive structure. All incentives are calculated over the 12 months of the trial and compared with the 12-month period immediately previous to the trial. The incentive payments apply to the percentage of change achieved across the group of enrolled patients at the level of the practice. The incentives supplement the existing payment arrangements. All incentives will be calculated and paid at the conclusion of the 12-month trial.

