### Outcomes

The primary outcome of the trial is relational continuity, as measured in the appropriate scale of the 43-item shortened Primary Care Assessment Tool (PCAT) [34]. The domains of accessibility, coordination and comprehensive care in participants will also be measured using the relevant domain scales of the PCAT [34].

We will assess the use of care-related services in the 12 months prior to the trial in comparison with the 12-month trial period. Data elements include:total prescription counts per patient and Pharmaceutical Benefits Scheme (PBS) costs;selected pathology services (microscopy, culture and sensitivity testing for leg ulcer swabs or urine, full blood count, erythrocyte sedimentation rate, thyroid function tests, prostate specific antigen and serum vitamin D level) per patient and Medical Benefits Schedule (MBS) costs;selected radiology services (lower back and chest x-rays, carotid duplex studies, computed tomography of the head) per patient and MBS costs; andtotal specialist referrals per patient and MBS costs.

We will also assess and collect data on hospitalisation and emergency department attendance rates in the 12 months prior to the trial in comparison with the 12-month trial period and for 5 years following the trial. Due to funding and time constraints, it is not possible to adequately power the trial to measure a reduction in PAHs within the study period. Therefore, the study investigators will establish linked data collection procedures to enable ongoing data collection and analysis for up to 5 years. Patient mortality rates will also be assessed for up to 5 years.

The proportion of patients seen within 1 week of discharge from hospital, and under 16-year-olds seen on the same day as requested for acute conditions, will be assessed using quarterly manual chart audits of enrolled patients in each practice performed by the PNs. In addition, patient/parent perceived ease of access will be measured by a brief survey at the beginning and conclusion of the trial, along with health-related quality of life (EQ-5D-5 L) [35]. Table 3 outlines the EQuIP-GP data variables, and Fig. 3 the program logic for the trial.

**Table 3 Tab3:** EQuIP-GP data variables

Data level	Variable	Dependent (DV) or independent variable (IV)	Source
Practice	Locality IRSD	IV	Australian Bureau of Statistics [28]
	Practice size - 6 or more GP FTEs	IV	Practice
	CIHI Practice survey^a^	IV	Practice
GP	CIHI Provider survey^b^	IV	GP

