Patient	EQ-5D-5 L baseline^c^	IV	Patient self-completion
	EQ-5D-5 L trial completion^c^	DV	Patient self-completion
	PCAT baseline (primary outcome measure)	IV	Patient self-completion [29]
	PCAT trial completion (primary outcome measure)	DV	Patient self-completion [29]
	Hospitalisations previous 12 months (emergency department [ED] + admission)	IV	Patient self-completion
	Hospitalisations during the trial (ED + admission)	DV	Patient self-completion
	Same day consultations <16 years previous 12 months	IV	Patient self-completion
	Same day consultations <16 years during the trial	DV	Patient self-completion
	1 week post-hospital consultations previous 12 months	IV	Patient self-completion
	1 week post-hospital consultations during the trial	DV	Patient self-completion
	DOB	IV	Electronic health record (EHR)
	Sex	IV	EHR
	Smoker	IV	EHR
	Indigenous	IV	EHR
	Diagnoses	IV	EHR
	Medication list number	IV	EHR
	Prescriptions previous 12 months	IV	EHR
	Prescriptions ordered during the trial	DV	EHR
	Pathology received previous 12 months	IV	EHR
	Pathology received during the trial	DV	EHR
	Imaging received previous 12 months	IV	EHR
	Imaging received during the trial	DV	EHR
	Chief diagnoses	IV	EHR
	Time from hospital discharge to appointment	IV	EHR
	Time from request for same day appointment (< 16 yo) to being seen	IV	EHR
	Consultation number	IV	EHR
	Consultation time length	IV	EHR
	Hospitalisations previous 12 months (ED + admission)	IV	EHR
	Hospitalisation during the trial (ED + admission)	DV	EHR
	Mortality during the trial	DV	EHR
	Hospitalisation previous 12 months (ED + admission)	IV	State hospital data
	Hospitalisation during the trial and 5 years following (ED + admission)	DV	State hospital data
	Prescriptions filled previous 12 months	IV	PBS
	Prescriptions filled during the trial and 5 years following	DV	PBS
	Pathology billed previous 12 months	IV	MBS
	Pathology billed during the trial and 5 years following	DV	MBS
	Imaging billed previous 12 months	IV	MBS
	Imaging billed during the trial and 5 years following	DV	MBS
	Specialist consultations previous 12 months	IV	MBS
	Other specialist consultations during the trial and 5 years following	DV	MBS
	Mortality during the trial and 5 years following	DV	Deaths registry

^a^Canadian Institute for Health Information (CIHI). Measuring Organizational Attributes of Primary Health Care Survey. Available at: https://www.cihi.ca/sites/default/files/info_phc_organize_en.pdf [Accessed 8 January 2019]

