### Data management

On receipt of their consent forms, all participants (practice and patient) will be assigned a code, which will link their data to a master-sheet which will contain participants’ demographic details and location. The master-sheet will be kept secure and confidential by the project coordinator in a password-protected file in the project data management system. All data for the evaluation of the project will be identified by the participants’ code only. This is so that the data can be kept confidential, but can be re-identified to enable appropriate grouping and analysis in the case studies at the end of the study. As general practices will be involved in the extraction of their own consultation time and access data, data extraction will be performed by a staff member of the practice who has usual access to the data.

All participants (practices and patients) will have the choice of providing their data in hard copy or online data collection forms. We will use ‘CloudStor’ as a secure, password-protected, cloud-based data collection and storage facility for participant-provided project research data [38]. The CloudStor server for the project is located in Australia. Permission for access to the data within the research team will be an only-if-needed basis. Hard copies of all consent forms will be stored in locked filing cabinets in the Departments of General Practice at each respective university (or password-protected folder on CloudStor if in soft copy form).

After data integrity checks, data extracts received from MedicineInsight will be stored in CloudStor. Data collected from the MBS, PBS, hospitalisation and deaths registries will be collected for 5 years following the trial, but only with express consent from the participants. These data will be stored and analysed in the Secure Unified Research Environment (SURE) maintained by the SAX Institute [39]. SURE is a purpose-built remote-access data research laboratory and storage facility with servers located in Australia.

Interview and IF diary data will be stored securely at each site during the collection period.

De-identification will take place after transcription of interviews. The code sheets and de-identified transcripts will be stored separately in CloudStor.

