### Quantitative data analysis

Baseline characteristics will be summarised at the collaborating PBRN centre and general practice levels within each trial arm, to provide counts and frequencies for categorical variables and means with standard deviations or medians and ranges for continuous variables, as appropriate. The primary outcome measure is a between-group difference in changes in the domain of relational continuity, as measured in the appropriate scale of the PCAT [34] at completion of the trial in comparison with baseline. Between-group differences in the domains of accessibility, coordination and comprehensive care in participants will also be measured and tested using the relevant domain scales of the PCAT [34]. To account for the potential effects of clustering, we will use hierarchical linear models with random main effects specified at the general practice level. Total prescription counts for the 12 months prior to trial commencement will also be used to control for case-mix across the trial.

Similarly, each of the other specified outcome variables (Table 2) will be statistically analysed using multi-level modelling methods to test for between-group (intervention vs. control) differences in the change in variables over the course of the study period. It is intended that data collection from administrative datasets (MBS, PBS and hospital admissions) will be continued beyond the trial period for 5 years, and analysed similarly. Data will not be excluded on the basis of non-adherence or protocol violation. The mixed models treat the data as missing at random and incorporate partial datasets, and are appropriate for analysis of datasets with missing data.

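### Hospital events and one-week review taken from practice records depend on the practice learning of the event, which can be expected to differ by arm in an unknown direction

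*Protocol article*

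**What the plan says.** Table 3 lists trial-year hospitalisation and emergency department (ED) attendance as a dependent variable from three sources: patient self-completion, the EHR ("Hospitalisation during the trial (ED + admission") and State hospital data ("Hospitalisation during the trial and 5 years following (ED + admission"). Each source has a matching row for the previous 12 months; the EHR one reads "Hospitalisations previous 12 months (ED + admission". The protocol does not say which source carries the between-arm comparison.

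The section on quantitative data analysis states that "each of the other specified outcome variables (Table 2) will be statistically analysed" for between-group differences in change. Table 2 is the timeline, so Table 3 must be meant.

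On follow-up, the Outcomes section names "The proportion of patients seen within 1 week of discharge from hospital" and says that it "will be assessed using quarterly manual chart audits of enrolled patients in each practice performed by the PNs". It does not describe how discharges enter that audit. Table 3 also holds a patient-reported dependent variable for one-week post-hospital consultations. The EHR row for time from discharge to appointment is an independent variable.

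The Intervention section requires intervention practices to offer "a review visit within 7 days of admission to an emergency department or hospital, or after other significant health events". The Abstract confirms that timely follow-up after hospitalisation is paid for. The Discussion adds that the funding model also aims to reduce potentially avoidable hospitalisations (PAHs) and ED attendances. Control practices give usual care. Under the section on randomisation, everyone except the statistician knows the allocation.

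**The concern.** A general practice record holds the hospital events that reach the practice: through a letter, the patient's account or the practice's own enquiry. A practice that must review patients soon after a hospital contact has to find out about that contact first. The intervention thus acts on whether an event is recorded, as well as on whether it happens. Randomisation does not protect against this, because the difference arises after allocation and because of it.

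The follow-up proportion is the more exposed measure. A discharge followed by a review will normally be in the chart. A discharge that was neither reviewed nor reported cannot be found by an audit of that chart, so it leaves the denominator. The observed proportion is then inflated most where capture is poorest. The nurses doing the audit also know their practice's arm.

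At stake are the trial-year secondary comparisons of hospital use and of one-week review, the second being a direct target of the incentive.

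**Working it through.** The protocol gives no capture rate, so there is no stated figure to reproduce. The capture values and true follow-up proportions below are assumptions chosen to show a range.

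**1. EHR event counts.** Let c_I and c_C be the share of true events that reach the record in the intervention and control arms.

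Observed rate ratio = true rate ratio × c_I / c_C.

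With no true effect:
- 80% control, 90% intervention: 0.90/0.80 = 1.125
- 70% control, 90% intervention: 0.90/0.70 = 1.29
- 60% control, 90% intervention: 0.90/0.60 = 1.50
- reversed, 90% control, 70% intervention: 0.70/0.90 = 0.78

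With a true ratio of 0.80, the 70%/90% case shows 0.80 × 1.29 = 1.03; reversed, it shows 0.80 × 0.78 = 0.62.

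**2. Does the baseline year remove it?** Suppose capture before the trial is c_0 in both arms. The observed ratio of changes is the true ratio × (c_I/c_0)/(c_C/c_0), which is again the true ratio × c_I/c_C. The baseline cancels only itself. By Table 2 the EHR extract starts on 1 August 2017 and the intervention on 1 August 2018, so the baseline year precedes the incentive. The missing-at-random argument does not help either: an unrecorded admission enters the data as no event, not as a missing value.

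**3. Audited follow-up proportion.** Let f be the true proportion reviewed within a week (these are taken as always in the chart), and s the chance that an unreviewed discharge is recorded.

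Observed proportion = f / (f + (1 − f) × s).

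With f = 0.40 in both arms:
- s = 0.7 control, 0.9 intervention: 0.40/0.82 = 48.8% against 0.40/0.94 = 42.6%, a difference of −6.2 points
- s = 0.5 control, 0.8 intervention: 0.40/0.70 = 57.1% against 0.40/0.88 = 45.5%, a difference of −11.7 points
- s = 0.8 control, 0.5 intervention: +11.7 points

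**4. What happens to a true gain.** Suppose 30% are truly reviewed in control and 50% in intervention, with overall capture of discharges of 70% and 90%. The charts show 0.30/0.70 = 43% and 0.50/0.90 = 56%. A 20-point gain appears as about 13 points.

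**5. Direction.** Payment for review favours finding and recording events. Reward for fewer PAHs and ED attendances favours recording fewer. The Intervention section ties payment to percentage change at practice level against the previous year. Nothing in the protocol says which pull is the stronger.

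**The case against.** The strongest reply is that the protocol already holds the safeguard. State hospital data are listed for the previous 12 months, the trial year and five years beyond, and do not depend on what the practice hears. The powered PAH comparison concerns the five years after the trial, where Table 3 lists hospital events from State data only, and the protocol concedes that it cannot adequately power a PAH comparison within the study period. Patient-reported one-week consultations are likewise independent of the practice's knowledge. The choice of leading source might be left to a fuller document. If hospitals notify practices routinely, capture need not differ at all.

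Much of this stands, and it limits the point. A reader might infer that the trial has no sound hospital outcome; Table 3 shows otherwise. A reader might also infer that the EHR count is biased against the intervention. The documents do not support a fixed direction, because the model rewards fewer hospital events as well as prompt review. Nor do they show that the chart audit would hide a real improvement: step 4 gives attenuation. That detection differs is itself an inference from the design.

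What the reply does not remove is that the protocol itself makes the EHR count a dependent variable to be tested between arms and the practice's own chart audit the method for one-week review. It names no leading source for hospital events and no step that equalises their discovery across arms.

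**Conclusion.** The concern holds as a risk of arm-dependent ascertainment in two practice-record measures: trial-year EHR hospital events and the chart-audited proportion reviewed within a week. Under the assumed capture gaps of 10 to 30 points, a null effect on events would show as a rate ratio of about 1.1 to 1.5 if intervention practices record more, and below 1 if they record less. The audited proportion would move by about 6 to 12 points in either direction. These figures illustrate the mechanism; they do not estimate its size in this trial. They rest on assumed capture, on reviewed discharges always being in the chart, and on the audit having no outside list of discharges.

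Because the direction is unknown, a reader of the results could not correct for it, which is the main reason to prefer a source that does not depend on the practice. The PCAT primary outcome and the sample size are not affected.

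**What to change.** - Name State hospital data as the lead source for the between-arm comparison of admissions and ED visits in the trial year, with the previous 12 months from the same source as baseline. Keep EHR and self-reported counts as supportive.
- For one-week review, use State-recorded discharges in consenting patients of both arms as the denominator, with visit dates from the EHR. The consultation rows that Table 3 draws from the Medicare Benefits Schedule concern specialists, so GP visit dates from that source cannot be assumed. Where the merge is not possible, treat the audited proportion as supportive and read it beside the patient-reported variable already in Table 3.
- Report by arm the EHR capture (EHR events divided by linked events) and the linkage-consent rate.
- Correct the table reference in the analysis section from Table 2 to Table 3.

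The linkage is already planned, but the change is more than wording. Results wait for linkage. Linked data are available "but only with express consent from the participants", and patients are recruited after practices are randomised with allocation known, so consent may itself differ by arm. This is why State data should lead and not be the only source. The review measure also needs patient-level merging: by the section on data management, linked data sit in the SURE environment and the MedicineInsight extracts in CloudStor.

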**Fig. 3 Fig3:**
[figure not shown]
EQuIP-GP program logic

### Qualitative substudy

The aim of the qualitative component is to provide context and insight into the experience, acceptability and success of the intervention from the perspective of patients, GPs and PMs. A case study methodology will be used. It is recommended in health research when studying complex phenomena and the context in which they are embedded [36]. The methodology is useful for conducting evaluations and developing interventions, both of which are relevant for this study. The constructivist underpinnings of case study methodology privilege the existence of multiple perspectives and subjective meanings [37], making it ideal to investigate the experiences of different staff members and patients within the same practice. Here, the ‘case’ to be examined at each practice is the uptake and implementation of an intervention using financial incentives.

The qualitative component combines interviews and the IF’s diary records. Semi-structured interviews will be conducted over the telephone or may be conducted in person if requested and where logistically viable. A total of 60 interviews (24 with patients, 24 with GPs and 12 with PMs) will be conducted – 30 at baseline and 30 at the conclusion of the 12-month trial. These will be divided evenly across the three collaborating PBRNs and conducted in intervention practices only. The case study sites will be purposively sampled using SEIFA code and practice size as descriptors to ensure diversity. A maximum variation approach to sampling of patients (age, gender, comorbidities) will be applied to invitation for the qualitative interviews.

### Data management

On receipt of their consent forms, all participants (practice and patient) will be assigned a code, which will link their data to a master-sheet which will contain participants’ demographic details and location. The master-sheet will be kept secure and confidential by the project coordinator in a password-protected file in the project data management system. All data for the evaluation of the project will be identified by the participants’ code only. This is so that the data can be kept confidential, but can be re-identified to enable appropriate grouping and analysis in the case studies at the end of the study. As general practices will be involved in the extraction of their own consultation time and access data, data extraction will be performed by a staff member of the practice who has usual access to the data.

All participants (practices and patients) will have the choice of providing their data in hard copy or online data collection forms. We will use ‘CloudStor’ as a secure, password-protected, cloud-based data collection and storage facility for participant-provided project research data [38]. The CloudStor server for the project is located in Australia. Permission for access to the data within the research team will be an only-if-needed basis. Hard copies of all consent forms will be stored in locked filing cabinets in the Departments of General Practice at each respective university (or password-protected folder on CloudStor if in soft copy form).

After data integrity checks, data extracts received from MedicineInsight will be stored in CloudStor. Data collected from the MBS, PBS, hospitalisation and deaths registries will be collected for 5 years following the trial, but only with express consent from the participants. These data will be stored and analysed in the Secure Unified Research Environment (SURE) maintained by the SAX Institute [39]. SURE is a purpose-built remote-access data research laboratory and storage facility with servers located in Australia.

Interview and IF diary data will be stored securely at each site during the collection period.

De-identification will take place after transcription of interviews. The code sheets and de-identified transcripts will be stored separately in CloudStor.

### Quantitative data analysis

Baseline characteristics will be summarised at the collaborating PBRN centre and general practice levels within each trial arm, to provide counts and frequencies for categorical variables and means with standard deviations or medians and ranges for continuous variables, as appropriate. The primary outcome measure is a between-group difference in changes in the domain of relational continuity, as measured in the appropriate scale of the PCAT [34] at completion of the trial in comparison with baseline. Between-group differences in the domains of accessibility, coordination and comprehensive care in participants will also be measured and tested using the relevant domain scales of the PCAT [34]. To account for the potential effects of clustering, we will use hierarchical linear models with random main effects specified at the general practice level. Total prescription counts for the 12 months prior to trial commencement will also be used to control for case-mix across the trial.

Similarly, each of the other specified outcome variables (Table 2) will be statistically analysed using multi-level modelling methods to test for between-group (intervention vs. control) differences in the change in variables over the course of the study period. It is intended that data collection from administrative datasets (MBS, PBS and hospital admissions) will be continued beyond the trial period for 5 years, and analysed similarly. Data will not be excluded on the basis of non-adherence or protocol violation. The mixed models treat the data as missing at random and incorporate partial datasets, and are appropriate for analysis of datasets with missing data.

